**Figure 2 fig0002:**
[figure not shown]
VCISpain (Video Classification of Intubation).

Simultaneously, a second anesthesiologist observes the tracheal intubation procedure and independently records the VCI score to assess interobserver reproducibility.

Complications will be prospectively recorded based on predefined clinical criteria, including:^25^ Hypoxemia (SpO_2_ < 90% for ≥ 10 seconds); Esophageal intubation (confirmed by capnography or clinical signs); Dental injury (visible tooth damage); Laryngeal trauma (presence of blood on the blade or tube, hoarseness, or stridor); Bronchospasm or laryngospasm (clinically diagnosed); Failed intubation (requiring a change in device or technique).

If a serious adverse event related to the videolaryngoscope is suspected, the attending physician may temporarily suspend the patient’s participation in the study. Throughout the process, patient safety is prioritized, and each center's standard protocols will be followed in the event of any incident.

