#### Secondary outcomes

1.The correlation between the Percentage of Glottic Opening (POGO) score and the difficulty of tracheal intubation.2.The impact of operator experience on VCI scale outcomes, including the influence of training level and prior videolaryngoscopy experience on interobserver agreement and VCI scoring.3.The incidence of tracheal intubation–related complications. While complications such as hypoxemia and laryngeal trauma are included as secondary outcomes, their expected low frequency means that related analyses will remain exploratory and descriptive in nature.

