### Exploratory data

The study will collect essential data in the following domains (Table 1) (Appendix 3):1)Patient Demographics: Includes age, sex, weight, height, Body Mass Index (BMI), and ASA status.2)Operator Characteristics: Documents the experience of the intubator or observer categorized by role (resident or specialist), years of experience (< 4, 4–8, > 8), and the number of prior intubations with VL: < 25, 25–50, > 50.3)Procedure Setting: Documents the clinical environment, including operating theater, ICU, Post-Anesthesia Care Unit (PACU), or emergency department.4)Videolaryngoscope Characteristics: Captures the type of videolaryngoscope used during the procedure.5)Data Related to the VCI Scale: a) VCI score: Includes blade type (Macintosh or hyperangulated), POGO (categorized as < 25%, 25%–50%, 50%–75%, > 75%), and difficulty (easy, difficult, failed); b) Rescue Devices: If a rescue device is used, a new VCI score will be recorded.6)Complications: these include hypoxemia, esophageal intubation, dental injury, laryngeal trauma, bronchospasm or laryngospasm, and failed intubation.

**Table 1 tbl0001:** CRF VCISpain. VIDEO CLASSIFICATION OF INTUBATION VCISpain – Case Report Form (CRF).

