**Complications**	
Desaturation	< 92%
Esophageal intubation	Yes / No
Dental damage	Yes / No
Other	Specify

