### Data management workflow

Initial Data Capture: after each procedure, the anesthesiologist will complete the CRF, recording demographic data, procedure variables, and any observed complications.•Data Transfer to REDCap: the pseudo-anonymized data will be entered into the secure REDCap platform. Each patient will be assigned a unique encoding code that is not directly linked to their personal information, ensuring confidentiality.•Ethical and Regulatory Compliance: all data will be collected and stored in full compliance with Good Clinical Practice (GCP) guidelines and current data protection regulations.

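### Hypoxemia is defined as SpO2 below 90% for at least 10 seconds, but the CRF as printed records only desaturation below 92%, with no duration

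*Protocol article*

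**What the plan says.** The complications paragraph in the Methods (under the intervention section, after Figure 2) states: "Complications will be prospectively recorded based on predefined clinical criteria". The first criterion listed is "Hypoxemia (SpO_2_ < 90% for ≥ 10 seconds", so the definition has two parts, a threshold and a minimum duration.

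The third secondary outcome is "The incidence of tracheal intubation–related complications". The same item continues: "While complications such as hypoxemia and laryngeal trauma are included as secondary outcomes", and then "their expected low frequency means that related analyses will remain exploratory and descriptive in nature". The Exploratory data section includes hypoxemia among the data to be collected: "Complications: these include hypoxemia, esophageal intubation, dental injury, laryngeal trauma, bronchospasm or laryngospasm, and failed intubation".

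The Data management workflow section makes the form the source of these data: "the anesthesiologist will complete the CRF, recording demographic data, procedure variables, and any observed complications". In the Complications block of Table 1, which is titled as the CRF, the only oxygenation row reads "Desaturation < 92" (per cent). No duration is printed and no field for the lowest value is shown. The rows for esophageal intubation and dental damage carry a yes/no response, and a last row allows another complication to be specified.

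**The concern.** The article prints both an outcome definition and the instrument meant to capture it, and the two describe different events. The threshold differs (90% against 92%), and so does the duration rule (at least 10 seconds against none). No part of the article reconciles them. This is not a detail left to a fuller document, because both versions are on the page.

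At stake is the hypoxemia part of the complication incidence. A descriptive rate depends entirely on its case definition, and no model or comparison offsets a numerator that counts something else. If the form in use is the one printed, the information needed to classify a patient under the text definition is not systematically kept, and analysis cannot restore it.

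**Working it through.** The article states no figure for hypoxemia, so there is nothing to reproduce. The check is a comparison of the two definitions.

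**Inputs**

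| Element | Methods text | Table 1, CRF |
|---|---|---|
| Name of event | Hypoxemia | Desaturation |
| Threshold | SpO2 < 90% | < 92% |
| Minimum duration | ≥ 10 seconds | none printed |
| Lowest SpO2 | not applicable | no stated field |

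**Step 1: does the text event imply the CRF event?** Yes. A patient whose SpO2 is below 90% for 10 seconds or longer has also been below 92%.

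**Step 2: does the CRF event imply the text event?** No. Two kinds of episode meet the CRF row and fail the text definition:
- a lowest value of at least 90% but below 92%, for any length of time;
- a fall below 90% that lasts less than 10 seconds.

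**Step 3: consequence if every site records fully at the printed threshold.** Let A be the number of patients who meet the text definition, and B the number who meet only the CRF row. The form then yields

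count recorded = A + B, with B ≥ 0,

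so A ≤ count recorded. The ratio of the recorded to the defined incidence is (A + B)/A = 1 + B/A when A > 0. Nothing in the article gives B/A, and the printed row does not separate A from B. The defined incidence could lie anywhere from zero to the recorded rate.

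**Step 4: consequence if sites differ.** The Pre-data collection preparations section says the training covered both the protocol and completion of the CRF. The Discussion gives 35 hospitals. Some investigators may tick the row only when the text criterion is met, and others whenever SpO2 drops below 92%. The pooled count is then A plus an unknown part of B, and nothing on the form shows which rule was applied.

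**Step 5: what else depends on the item.** The primary outcome is agreement on the VCI score between operator and observer. The Sample size section rests on kappa, with an assumed incidence of difficult intubation as a second consideration. Neither uses hypoxemia. The other two secondary outcomes, POGO against difficulty and the impact of operator experience on VCI outcomes and agreement, do not use it either.

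**The case against.** The strongest reply is that little rests on this item. The article itself limits complication analyses to exploratory description, and the primary analysis does not touch them. That stands, and it sets the grade of the point. It does not remove the contradiction, because a descriptive incidence still needs one definition.

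A second reply is that the working form may hold more than the table shows. Appendix 3, cited alongside Table 1, and the REDCap form are not shown. The desaturation row lacks the yes/no response printed for its neighbours, so it could be a tick box or a value entry. The specify line could also carry detail. This is fair as far as it goes, and it is why the point is made about the form as printed. Optional free text is not systematic capture, and if the working form differs, the published table needs correcting.

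Three stronger readings are tempting but not supported:
- **A certain overcount.** A reader might infer that hypoxemia will certainly be overstated. That follows only if every site records fully at 92%. Under-recording, or use of the text criterion at some sites, is equally compatible with the article.
- **A specific inflation factor.** The article contains no SpO2 distribution, so any multiple would only restate an assumption about B/A.
- **A mislabelled publication.** No section says how the result will be labelled. Reporting a rate below 92% as hypoxemia is a risk, not a stated intention. Calling it desaturation would be accurate, but would leave the defined component unreported.

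**Conclusion.** The point holds as an internal inconsistency between the outcome definition and the printed data-capture form. On the form as printed, protocol-defined hypoxemia cannot be derived. The recorded count is an upper bound on it if sites follow the form completely, and a mixture of two definitions if they do not. The size is unknown. The effect is confined to one component of a descriptive secondary outcome and does not reach the kappa analysis, the sample size or the other secondary outcomes. It is a moderate correction, not a threat to the study's main conclusion.

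This rests on two assumptions: that Table 1 is the form in use, as its title says, and that no unseen field records the lowest SpO2 and the duration.

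**What to change.** Reconcile the complications paragraph and the Table 1 row to one outcome definition that states both threshold and duration. Two routes remove the contradiction, and the choice between them is the investigators':

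1. **Align the text to the item collected.** State the outcome as the event the form records, under the form's name, and date the change before complication data are summarised. This costs a short correction and needs no new field. The previously defined event is then no longer reported.
2. **Change the CRF and REDCap item.** Record the lowest SpO2, and a yes/no for whether the minimum duration below the chosen threshold was met, naming that threshold in the item. The defined event can then be derived from that point on. The cost is more than a field edit. Recruitment was due to start in September 2024 and the packages had already gone to the hospitals, so the form must be redistributed and explained again. The data then fall into two recording periods that must be reported separately.

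Under either route, report records already taken on the printed form as desaturation below 92%, not as protocol-defined hypoxemia. Ask sites which rule they have applied to that row, and state the answer with the rate. If Appendix 3 or the REDCap form already captures the level and duration, correcting Table 1 is enough.

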### Intervention in the VCISpain study

The intervention begins during the pre-anesthetic consultation or in the anesthetic-surgical preparation area (preoperative holding area), where eligible patients are provided with a detailed information sheet outlining the study objectives, methodology, and potential risks. The investigator anesthesiologists explain the protocol, address any questions or concerns, and ensure patient understanding before obtaining written informed consent.^24^ Participants are informed of their right to withdraw consent at any time. If consent is withdrawn, the participant’s data will be excluded from analysis in accordance with ethical guidelines, thereby respecting their autonomy (Appendices 1–2).

The clinical procedure follows standard practices (Fig. 1). TI is performed using a videolaryngoscope selected based on patient characteristics and the resources available at each center. The responsible anesthesiologist evaluates the TI using the VCI scale, which comprises the following components (Fig. 2):^22^1.Blade Type: The videolaryngoscope is classified as either Macintosh (M) or hyperangulated (H).2.Percentage of Glottic Opening (POGO): The POGO score is recorded at a standardized time point ‒ immediately before advancing the endotracheal tube into the glottis. This measurement reflects the actual glottic view under the force and positioning used during intubation. Investigators are instructed not to record the initial or best view, but rather the view observed at the moment of tube insertion, to ensure consistency and clinical relevance.3.Ease of Intubation: This is categorized as easy (E), difficult (D), or failed (F).a)Easy refers to successful tracheal intubation using the manufacturer’s standard technique for the selected videolaryngoscope, without the need for adjuncts or external assistance.b)Difficult is defined as intubation requiring the use of adjuncts such as a bougie, stylet, or other guiding devices to facilitate tube placement.c)Failed refers to the inability to intubate the trachea using the initially selected videolaryngoscope, necessitating the use of a different videolaryngoscope or an alternative device (e.g., fiberoptic bronchoscope, supraglottic airway, or surgical airway).

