### Data collection and management

Data will be collected using a standardized and anonymized physical CRF, independently completed by both the intubating anesthesiologist and the observer during and immediately after the intubation procedure. The collected data will then be managed through the secure electronic platform Research Electronic Data Capture (REDCap), hosted at the University of Navarra (UNAV), ensuring stringent patient confidentiality and data integrity. REDCap offers validated data capture and a transparent audit trail through its comprehensive logging features.

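### Laryngeal trauma and bronchospasm/laryngospasm are predefined complications with no dedicated field on the printed CRF, and hoarseness and stridor have no stated time at which they would be recorded, so their incidence is likely to be under-counted

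*Protocol article*

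**What the plan says.** In the protocol article, Secondary aims, the third aim is the incidence of complications of videolaryngoscopic intubation. Secondary outcomes repeats it, naming hypoxemia and laryngeal trauma as examples, and adds that these analyses will be exploratory and descriptive because few events are expected.

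The complications paragraph after Figure 2 (within Intervention in the VCISpain study) sets out six items under predefined criteria. They include "Laryngeal trauma (presence of blood on the blade or tube, hoarseness, or stridor"), "Bronchospasm or laryngospasm (clinically diagnosed") and "Failed intubation (requiring a change in device or technique"). Item 6 of Exploratory data lists the same six as data the study will collect: "these include hypoxemia, esophageal intubation, dental injury, laryngeal trauma, bronchospasm or laryngospasm, and failed intubation".

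The complications block of Table 1, which is presented as the study's CRF, has four rows: desaturation, esophageal intubation, dental damage, and *Other* with the prompt *Specify*. Failed intubation is not in that block. It is an option of the ease-of-intubation item, which the intubator and the observer each complete.

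On timing, Data collection and management has the CRF completed "during and immediately after the intubation procedure". Data management workflow says the anesthesiologist completes it after each procedure and includes any complications observed.

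**The concern.** An incidence needs a case definition, a moment at which the case can be seen, and a record that separates *no* from *not considered*. For laryngeal trauma the last is missing and the second is met for only one of the three signs. For bronchospasm/laryngospasm the last is missing.

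Free text relies on the clinician remembering that an item is of interest. A patient with nothing written may have been free of the event or may never have been considered for it, so the denominator of assessed patients is unknown. Hoarseness and post-extubation stridor arise once the tube is out, after the only recording time the article gives. Both problems push the count down, and no later analysis can recover signs that were never written down. At stake is whether the reported rates can be read as incidences at all, and whether they can be compared with those for the ticked items on the same form.

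**Working it through.** The protocol states no figure on this point, so there is none to reproduce. The check sets definition, collection list, form and timing side by side.

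**Step 1. Six complications against the CRF in Table 1.**

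| Predefined complication | Where the CRF records it |
|---|---|
| Hypoxemia | Named row (desaturation), with a different threshold |
| Esophageal intubation | Named row, yes/no |
| Dental injury | Named row, yes/no |
| Laryngeal trauma | Free text under *Other* only |
| Bronchospasm or laryngospasm | Free text under *Other* only |
| Failed intubation | Not in the block; recorded by the ease-of-intubation item |

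Count: 3 with a named row, 1 recorded elsewhere on the form, 2 with free text only (3 + 1 + 2 = 6). The hypoxemia row shows a separate mismatch of the same kind: the text requires saturation below 90% for at least 10 seconds, while the CRF row gives below 92% with no duration. Those two places also need to be reconciled.

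**Step 2. Three laryngeal-trauma signs against the recording time.**

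- Blood on blade or tube: visible during and just after intubation.
- Hoarseness: needs the patient to phonate, which is not possible with the tube in place.
- Stridor: post-extubation stridor has not yet occurred.

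One of three signs fits the stated time. The workflow wording (after each procedure) does not clearly extend it, and no post-extubation visit or check is described.

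**Step 3. Size.** Let s be the share of laryngeal-trauma cases that show only as hoarseness or stridor. If those are missed and all others are recorded, reported incidence = (1 − s) × true incidence, so the relative shortfall equals s. The documents give no value for s. Assuming 25% returns a 25% shortfall and assuming 75% returns 75%; the result only repeats the assumption. The direction is firm and the amount is not estimable. Free-text under-reporting adds to it, also by an unknown amount.

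**Step 4. Failed intubation.** The VCI scale says "Failed refers to the inability to intubate the trachea using the initially selected videolaryngoscope, necessitating the use of a different videolaryngoscope or an alternative device". The complications list says "Failed intubation (requiring a change in device or technique"). The second adds the word technique. The scale also says "Difficult is defined as intubation requiring the use of adjuncts such as a bougie, stylet, or other guiding devices to facilitate tube placement". Adding an adjunct with the same videolaryngoscope is therefore Difficult on the scale, yet could loosely be called a change of technique. The printed CRF has only one structured record of failure, the VCI item, so the form itself yields no second failure rate.

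**The case against.** **The events can still be recorded.** This stands in part. The free-text row can hold blood on the blade or a spasm, so a reader who infers that these complications cannot be counted goes too far. What remains is that a blank is not a *no*.

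**The form is not said to close.** This is correct. The article gives a completion time and no lock, so it would be wrong to say that the CRF shuts before hoarseness can appear. The laryngeal-trauma definition can also be met by blood alone. But no occasion for the other two signs is described.

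**A condensed article may not show the whole instrument.** Appendix 3 and the REDCap form are not shown and may contain more fields. However, Table 1 is offered as the CRF and does not match the text of the same article, so this is more than an omission through shortening.

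**Failed intubation has two conflicting definitions.** A reader might infer this stronger point, with sizeable miscounting. With about 1,325 evaluable patients (1,395 × 0.95 = 1,325.25), the Introduction's 0.05%–0.35% failure range gives 0.7 to 4.6 cases, and its more recent 0.06 per 1,000 gives about 0.08. The 10% difficult intubation assumed under Sample size gives about 133 (1,325 × 0.10 = 132.5) that might be swept in. The documents do not support this. The parenthesis qualifies an intubation that has failed, and does not turn a successful adjunct-assisted one into a failure. The scale's own examples of failure, such as a supraglottic or surgical airway, are naturally changes of technique. What stands is loose wording that is easily aligned.

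**The outcome is only descriptive.** This is true and limits the weight of the point, but a descriptive rate still depends on complete capture.

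**Conclusion.** The point holds in a limited form. Two of six predefined complications have no dedicated field on the CRF shown, and two of the three signs defining one of them have no stated occasion for recording. Followed as written, the plan would under-count laryngeal trauma and probably bronchospasm/laryngospasm. The size cannot be given from the documents.

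This assumes that Table 1 is the CRF in use, that no unshown appendix or electronic form adds these fields, and that no post-extubation check exists outside the article. If any of these is wrong, the point shrinks accordingly.

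The effect is confined to the third secondary aim, which is descriptive. The kappa for agreement between intubator and observer does not use the complications block and is unaffected. The failed-intubation wording is a minor matter of alignment.

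**What to change.** 1. Add yes/no fields to the CRF and REDCap for laryngeal trauma and for bronchospasm/laryngospasm, so that absence is recorded explicitly.
2. Report laryngeal-trauma incidence as blood on blade or tube only, and state that hoarseness and stridor were not ascertained.
3. Derive the failed-intubation count from the VCI category Failed and align the complications wording with the scale's definition. Since both raters complete that item, state whose rating supplies the count.

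The cost is a form edit and a short text correction. The laryngeal-trauma endpoint becomes narrower but measurable. Recruitment was planned to start in September 2024; if patients are already enrolled, ascertainment will differ before and after the edit. The two periods should then be reported separately, with the earlier one described as free-text capture.

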### Outcome measures

#### Primary outcome

The primary outcome is the inter-rater agreement and reproducibility of the VCI scale, defined as the level of concordance between the VCI scores assigned by the anesthesiologist performing the tracheal intubation and an independent observer.

